#### ***3.10.2. Passive follow up (6 months after the first active follow up)***

Patients identified as treatment failures (clinical and parasitological) within the first follow up of 28 days will be treated with a full course of quinine or any other appropriate oral treatment (unrelated to the study drugs). Parents/guardians of children who have either been treated or classified as ACPR, i.e. with no malaria infection at day 28 of the first follow up will be asked to attend the health facility whenever the child is sick for the next 6 months. Each child will be visited monthly at home to keep the contact with the health facility. However, no data or blood slide will be collected unless the child is sick. Any attendance of children belonging to the cohort recruited for the first follow up will be recorded. The child will be clinically assessed and the medical history will be taken. Body temperature and a blood sample for

parasitaemia, Hb and PCR will be systematically collected. A diagnosis will be made and the child treated accordingly. Whenever an episode of uncomplicated malaria is diagnosed, the inclusion and exclusion criteria (section 3.8) will be checked and if these are fulfilled, the child will be re-treated with the same drug received for the first episode and will be followed up for the next 28 days (second active follow-up) with the same methodology as the first active follow-up. After the second active follow up, even if the child attend with an episode of clinical malaria fulfilling the inclusion/exclusion criteria, s/he will be treated with the local first line drug and no active follow up will be carried out after treatment. Children with a malaria infection but not fulfilling the inclusion and exclusion criteria will be treated with the local first line drug and their parents will be informed that they are still part of the cohort under passive surveillance. Children will reach the end of the study at the end of the 6-month passive follow up when they will be visited at home and the parents/guardians will be informed that the study is finished (Appendix VIII).

### ***3.11 Randomisation and treatment allocation***

A randomisation list of blocks of varying size and stratified according to the number of recruitment points in each site will be provided by the Centre for Medical Statistics and Health Evaluation/ University of Liverpool. Sealed envelopes labelled with the patients unique code and containing the treatment allocated to the patient will also be provided by Liverpool according to the above mentioned list. This will guarantee concealment as the envelope will be opened only after recruitment.

### ***3.12 Treatment administration***

The study treatment will be administered by health workers under the direct supervision of a licensed physician. The correct number of tablets will be determined using the weight dosing chart. If necessary the study drugs (either whole or as fractions) will be crushed, dissolved in water and squirted into the mouth using a syringe without needle. Administration of all treatments, including AL will be directly observed. After drug administration, patients will be kept for one hour in the clinic. A dose will be repeated in full if vomiting occurs within 30 minutes of administration and halved if vomiting is between 30 minutes and 1 hour post dosing. This event will be documented in the case record form (CRF). If vomiting persists, the patient will be withdrawn from the study and treatment changed (e.g. quinine).

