## 2. TRIAL OBJECTIVES AND PURPOSE

The main objective is to compare the safety and efficacy of 4 artemisinin-based combination therapies (ACT), i.e. amodiaquine-artesunate (AQ+AS), artemether-lumefantrine (AL), dihydroartemisinin-piperaquine (DHAPQ), chlorproguanil-dapsone-artesunate (CDA), for single and repeat treatments of uncomplicated malaria in African children. Safety will be determined by registering adverse events and grading, laboratory, and vital signs evaluations. Their incidence will be compared between the different study arms.

Specific objectives are the following:

1. To evaluate the efficacy of the 4 ACTs for the treatment of children with uncomplicated *P. falciparum* malaria (first active follow-up);
2. To determine after the first active follow-up the incidence rate of a second clinical episode of uncomplicated *P. falciparum* malaria;
3. To evaluate the efficacy of treating the second clinical episode of uncomplicated *P. falciparum* malaria with the same ACT used for the first one (second active follow-up);
4. To evaluate during the active and passive follow up the safety of the 4 ACTs for the treatment of children with uncomplicated *P. falciparum* malaria;
5. To establish the impact of using CDA on the selection of *P. falciparum* genotypes linked to SP resistance.

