### **3.6 Statistical analysis**

Since the trial has been powered for equivalence at each site, interim analyses will be undertaken for each of the sites separately. Interim analyses will be undertaken by the trial statistician and presented to the DSMB every 6 months during recruitment while safety monitoring will be continuous. A detailed analysis plan will be drawn up prior to the first interim analysis.

For each analysis, both an intention-to-treat, a per-protocol and a CACE approach will be adopted. Patients in each treatment group in each site will be described separately with respect to baseline characteristics. The clinical importance of any imbalance will be noted though statistical tests of significance will not be undertaken.

For the analysis at each site, and for the primary outcomes relating to treatment failure, the relative treatment effect will be summarised in terms of the risk difference and associated confidence interval for each pairwise combination of treatments.

For the combination of data across sites, a meta-analytic approach will be employed. The six pairwise comparisons of treatments will be undertaken, stratified by site. Heterogeneity due to patient-level and site-level characteristics will be investigated. Finally, all data will be entered into a regression model and a network meta-analytic approach adopted.

If appropriate, logistic regression will be used to examine the effect of prognostic factors on the primary outcome. Tests of interaction between baseline characteristics and treatment will be kept to a minimum.

Adverse events will be grouped according to a pre-specified side-effect coding system and tabulated. The number (and percentage) of patients experiencing each adverse event will be compared across treatment groups. The number (and percentage) of occurrences of each adverse event will also be compared across treatment groups.

Every effort will be made to minimise the amount of missing data in the trial. However it is realistic to assume a priori that missingness may be informative. Whenever possible, information on the reason for missing data will be obtained. Sensitivity analyses, including imputation, will be undertaken to assess the robustness of the conclusions to the missing data.

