## **4. CONCOMITANT THERAPIES**

### ***4.1 Disallowed Concomitant Drug Therapies during the active follow ups***

Any antimalarial, or antibiotic with antimalarial activity (erythromycin or other macrolides, co-trimoxazole or other sulfonamides, any tetracycline including doxycycline, and quinolones, clindamycin). Intake of these drugs leads to withdrawal of the patient from the ongoing active follow up. However, the patient will be kept in the passive follow up and when presenting with another clinical malaria episode fulfilling the inclusion/exclusion criteria, another active follow up can be started. Drugs known to cause haemolysis (e.g. sulpha drugs) should not be administered in children in the CDA arm. There are no disallowed concomitant therapies during the passive follow up.

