### **5. PATIENT WITHDRAWAL CRITERIA**

Patients will be excluded from further assessment if there is withdrawal of informed consent. Severe adverse events related to the study drug are also a reason for withdrawal from the study drug but not withdrawal from study follow-up.

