### **6. PROTOCOL VIOLATIONS**

A protocol violation occurs when an event happens that does not allow for accurate interpretation of response to treatment. Protocol violations will be defined in the statistical analysis plan. All patients should be followed up until the end of the passive follow up unless fulfilling the study withdrawal criteria.

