#### ***7.1.5 Length of follow-up for adverse events***

**AEs presenting during the active follow-up period:** A patient still experiencing an AE at the end of the active follow up, i.e. at day 28 will be managed as follows:

- If the AE has been detected and reported before the last visit and
  - it is mild (Grade 1), the patient will be managed according to good medical practice and the active follow up will be stopped. The end date for the AE will be recorded as Day 28.
  - Its grade is more than, the patient will be followed until the AE resolves, improves, or stabilizes.
- If the AE is new, the AE will be reported and the patient will be followed until the AE resolves, improves, or stabilizes.

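### Section 3.12 withdraws a persistently vomiting child from the study, whereas section 4.1 keeps a child given another antimalarial in passive follow-up

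*Protocol*

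**What the plan says.** Section 3.12 (Treatment administration) covers a vomited dose: repeat it in full or by half according to timing, and document the event in the CRF. It then adds: "If vomiting persists, the patient will be withdrawn from the study and treatment changed (e.g. quinine").

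Other sections bear on the same child:

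- **Section 4.1** lists any other antimalarial as disallowed during active follow-up. Taking one ends the ongoing active follow-up. "However, the patient will be kept in the passive follow up", and a later qualifying episode can open another active follow-up.
- **Section 4.4** stops active follow-up for treatment failures, gives quinine or the national alternative, and still counts the child in the six-month passive follow-up.
- **Section 5** (Patient withdrawal criteria): "Patients will be excluded from further assessment if there is withdrawal of informed consent". It adds: "Severe adverse events related to the study drug are also a reason for withdrawal from the study drug but not withdrawal from study follow-up". Vomiting is not mentioned.
- **Section 6**: "All patients should be followed up until the end of the passive follow up unless fulfilling the study withdrawal criteria".
- **Section 3.10.2** records any attendance by a child in the recruited cohort, schedules monthly home visits, and places the end of the study at the end of the six-month passive follow-up.

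**The concern.** Section 3.12 and section 4.1 give different answers for one child. Under 3.12 a child switched to quinine for vomiting leaves the study. Under 4.1 a child who has taken quinine leaves active follow-up and stays in passive follow-up.

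Passive follow-up is what is at stake. Objective 4 reads: "To evaluate during the active and passive follow up the safety of the 4 ACTs". Objective 2 (incidence of a second clinical episode) and objective 3 (re-treatment of that episode) both draw on the passive period. So do the secondary endpoints of section 3.3 that run beyond day 28. Section 3.6 states that "both an intention-to-treat, a per-protocol and a CACE approach will be adopted", and itself expects that missing data may be informative.

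Vomiting the assigned drug happens after randomisation and may depend on the drug. In an open-label trial comparing different drugs, removing children for that reason could remove them unequally by arm. With 10 sites, some may follow 3.12 and others 4.1, so identical children could be handled differently.

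**Working it through.** The contradiction rests on the text and needs no figure. The protocol states no vomiting rate, so there is no plan figure to reproduce.

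**Step 1. What the study means.** Section 3.10.2 ends it when the six-month passive follow-up ends. Leaving the study therefore includes leaving passive follow-up. The protocol also has terms for smaller exits: section 5 separates study drug from study follow-up, and section 4.1 names the ongoing active follow-up. Section 3.12 uses none of them.

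**Step 2. Trace one child.** A child vomits the dose and its repeat on day 0 and is switched to quinine.

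- Section 3.12: out of the study, passive follow-up included.
- Section 4.1: quinine is another antimalarial, so out of active follow-up but in passive follow-up.
- Section 5: no listed criterion is met, because consent stands.
- Section 6: followed to the end of passive follow-up, unless 3.12 is itself taken as a withdrawal criterion.
- Section 4.4: applies directly only if the child is a treatment failure, and then keeps the child in passive follow-up.

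The direct conflict is with 4.1. Sections 5 and 6 point the same way without naming vomiting, and 4.4 is a parallel rule.

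**Step 3. What 3.12 adds to the loss.** Active follow-up ends under 4.1 in any case. The extra loss under a literal 3.12 is passive follow-up only: sick visits, clinical malaria incidence, second episodes and safety information.

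**Step 4. Ceiling on that loss.** Inputs: 5100 children (section 3.1), six months of passive follow-up (sections 3.7 and 3.10.2), and an assumed rate of persistent vomiting at first treatment of 1% to 3%.

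- Children = 5100 × rate: 5100 × 0.01 = 51; 5100 × 0.03 = 153.
- Child-months = children × 6: 51 × 6 = 306; 153 × 6 = 918.

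These figures are reached only if every site follows 3.12 literally and each such child would otherwise have completed six months.

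**The case against.** The best defence is that the phrase is loose drafting and other text contains the damage. Section 3.12 does not tell sites to stop collecting data. Section 3.10.2 records any attendance by the recruited cohort and visits each child monthly, and a child switched to quinine belongs to that cohort. Section 6 has an exception for withdrawal criteria, which 3.12 could be read as supplying. Section 5 does not say that consent is the only ground. Its adverse-event sentence covers severe drug-related events, whereas Appendix I grades two or three vomiting episodes a day as moderate.

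Much of this stands. The child-months are a ceiling, and it would be too strong to say that sites were told not to collect these data. Section 5's adverse-event sentence supports the point only by analogy. So does section 7.1.5, whose rule that "the patient will be followed until the AE resolves, improves, or stabilizes" concerns events still present at day 28.

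The conflict with 4.1 remains. Treating 3.12 as an extra withdrawal criterion still collides with 4.1 once quinine is given, and the section headed as the withdrawal criteria omits it. Reading the study as active follow-up only is what 3.12 should say, but section 3.10.2 uses the term more widely.

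A reader might infer three stronger points that the protocol does not support:

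- **A drain on the day-28 sample size.** At 1% to 3%, 1.7 to 5.1 of 170 children per site-arm could be set against the 15 allowed for loss (170 − 155, section 3.5). But section 4.1 ends their active follow-up anyway, so correcting 3.12 recovers none of them at day 28.
- **A shift in the primary endpoints.** This needs an assumed rate, an excess in one arm, an assumed share with danger signs, and a withdrawal that erases an early failure already met. Section 3.2 defines early failure with no exception for withdrawn children, so nothing supports the last step.
- **A gap in the early-failure rule.** Persistent vomiting that amounts to an Appendix V danger sign, with parasitaemia on days 0 to 3, is already an early treatment failure under section 3.2. A dosing section need not repeat that.

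**Conclusion.** Wrong as written; minor severity. Section 3.12 contradicts section 4.1 on whether a child switched to another antimalarial stays in passive follow-up, and it sits against sections 4.4, 5 and 6. Taken literally, it gives up passive follow-up in randomised children for a possibly drug-related reason, and it invites inconsistent handling across sites.

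The size is uncertain and bounded: at most 51 to 153 children and 306 to 918 child-months. Both ranges rest on the assumed 1% to 3% and on literal compliance with 3.12 everywhere. Whether the loss would differ by arm cannot be determined from the protocol. The textual conflict does not depend on these assumptions.

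**What to change.** Replace the last sentence of section 3.12 with: 'If vomiting persists, study drug is stopped, treatment is changed (e.g. to quinine), and the child leaves the ongoing active follow-up but stays in passive follow-up, as in section 4.1; the early treatment failure criteria of section 3.2 still apply.'

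The cost is one sentence. Monthly home visits, recording of sick visits and CRF documentation of vomiting are already planned, so no new procedure is needed.

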## **4. CONCOMITANT THERAPIES**

### ***4.1 Disallowed Concomitant Drug Therapies during the active follow ups***

Any antimalarial, or antibiotic with antimalarial activity (erythromycin or other macrolides, co-trimoxazole or other sulfonamides, any tetracycline including doxycycline, and quinolones, clindamycin). Intake of these drugs leads to withdrawal of the patient from the ongoing active follow up. However, the patient will be kept in the passive follow up and when presenting with another clinical malaria episode fulfilling the inclusion/exclusion criteria, another active follow up can be started. Drugs known to cause haemolysis (e.g. sulpha drugs) should not be administered in children in the CDA arm. There are no disallowed concomitant therapies during the passive follow up.

#### **4.2 Allowed Concomitant Drug Therapies**

During the trial patients can be prescribed drugs e.g. paracetamol, and antibiotics with no known antimalarial activity (penicillins, cephalosporins). The dose, route, time and duration of any concomitant medical treatment will be recorded in the CRF.

#### **4.3 Special Conditions**

Parents or guardians will be discouraged from obtaining drugs from any other source such as private pharmacies, markets or clinics. Parents/guardians will be encouraged to bring their children to the study clinic if their child is unwell or if they are worried about their child's health.

#### **4.4 Rescue Treatments**

Active follow up of patients with treatment failure, including parasitological failure, will be stopped and they will be treated with rescue treatment. This consists in quinine 10 mg/kg orally three times a day for 7 days or an antimalarial treatment according to the country's national guidelines. Any patient, who is diagnosed with severe malaria or danger signs during follow-up, will be referred for treatment with parenteral quinine and supportive measures at the local facility or hospital. After the rescue treatment the patient will still be considered in the passive follow up until completion of the 6-month period.

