# 1. RATIONALE AND BACKGROUND

Resistance to commonly used antimalarial drugs represents the major drawback and obstacle for controlling malaria in endemic countries. Currently, the geographic distribution of *P. falciparum* resistance to chloroquine (CQ) almost corresponds to that of the parasite itself and it is severe in many countries. Several countries have changed their first line treatment from CQ to other regimens, usually sulfadoxine-pyrimethamine (SP), but resistance to the latter has rapidly reached critical levels in some areas of East and Central Africa and a public health disaster might be imminent. Unfortunately, only few available alternative drugs are ready for deployment. It is generally agreed that endemic countries should opt for combination treatment, i.e. the association of 2 or more antimalarial drugs with different metabolic targets. Artemisinin derivatives (AS) and consequently artemisinin-containing combinations (ACT) have several advantages as they produce a rapid clinical and parasitological cure, reduce gametocyte carriage rate and are generally well tolerated. In Africa, studies on ACT (artesunate with either CQ, amodiaquine (AQ) or SP) have been carried out in a few thousands children with uncomplicated malaria. Good safety and efficacy were reported when the partner drug was also efficacious. However, at least 2 of the 3 drugs mentioned above (CQ and SP) can no longer be considered as useful partner drugs for combination with AS because of their confirmed low efficacy. Several African countries have already opted for ACT (for example: Burundi for AQ+AS, Zanzibar for AQ+AS and artemether + lumefantrine (AL), Zambia for AL; Kenya, Rwanda, Uganda and Tanzania might or are about to change to AL), but additional information for their optimal deployment is still required. Besides a non-co-formulated AQ+AS, the only other possible alternative is AL, which is moderately expensive and has a complex dosage. The need to provide African Ministries of Health with reliable information on ACT safety, efficacy and effectiveness (NB, the latter is not addressed in this proposal) is obvious. We therefore propose to test 4 combinations, namely amodiaquine + artesunate (AQ+AS), dihydroartemisinin + piperaquine (DHAPQ), artemether + lumefantrine (AL) and chlorproguanil-dapsone + artesunate (CDA), the first 3 being co-formulated. The studies will be carried out in 7 African countries covering a variety of epidemiological situations. All partners involved are experienced in the conduct of clinical trials and most of them have been working in this field for several years. Moreover, the close relationship of institutions such as the EANMAT to the countries' Ministries of Health is a guarantee for the rapid uptake of the project's results for the review and modification of their national antimalarial drug policy.

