## 3. TRIAL DESIGN

### 3.1 Study Design

This is a multi- centre, randomized, open label, multi-armed study involving 10 investigational centres that will enrol 5100 patients, 510 per site, 170 per arm. The 4 combinations will be tested and compared in different countries, with different malaria transmission and resistance characteristics (Table 1). A three-arm trial maximises the amount of information collected and, at the same time, keeps the individual studies manageable.

The total number of patients treated by each study treatment will be between 1700 (DHAPQ) and 1020 (AQ+AS and CDA). For the comparisons between treatment arms, the highest number of patients per arm will be 1360 (DHAPQ vs AL), and the lowest 340 for the comparison between AQ+AS and CDA. This is slightly different from what had been planned in the proposal submitted to the EDCTP. The Rwandan collaborators have requested not to test AQ+AS on the ground that this combination will not be used as first or second line treatment. Indeed, resistance to AQ in Rwanda is already substantial, particularly in the site of Rukara. This is why the arm AQ+AS has been replaced by DHAPQ.

The main justification for not performing a double-blind study is the requirement to use the double-dummy technique requiring placebos for 3 arms drugs per site, resulting into a treatment schedule which would be very laborious for the patient. In order to ensure concealment of treatment allocation and avoid other biases, the following requirements will be assured:

- 1 The randomization list will be generated prior the beginning of the study. Treatment allocation will be concealed until the completion of the screening and the final recruitment of the patient (see section 3.10);
- 2 The interpretation of the PCR reading will be blinded/masked with regard to the treatment allocation of the patients (see section 3.9);
- 3 An independent Data Monitoring Board will review all efficacy and safety data (see section 13.2).

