All medication will be administered under observation by an authorised member of the study team (physician, clinician, or study nurse).

After the child has reached a study outcome, before or at the end (day 28) of the first active follow up, the parents or guardians will be encouraged to attend the health facility when the child is sick. If the child is not diagnosed with clinical malaria, s/he will be treated accordingly and parents or guardians will be asked to come back again whenever the child is sick. If the child has clinical malaria and meets the inclusion/exclusion criteria, s/he will be treated with the same drug received at the beginning of the first follow up and actively followed for 28 days according to the procedure outlined above. Re-treatment with the same study drug will be done at an interval of at least 29 days from the first treatment, i.e. after the first active follow up has finished. At the end of this second follow up, when one of the study

outcomes is reached, the child will be passively followed up until completion of the 6-month period started at the end of the first active follow up. Any malaria episode will be recorded and the patient treated with the standard antimalarial treatment. No active follow up will be carried out.

Patients will be assessed as summarized in the following flow-chart.

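### Sections 3.10.2 and 4.4 of the protocol give different rescue rules, and section 4.4 lets a child be rescued with the study drug that has just failed

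*Protocol*

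**What the plan says.** Two sections of the protocol tell a site how to treat a child who fails.

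- **Section 3.10.2 (Passive follow up)** deals with failures, clinical or parasitological, in the first 28 days. They receive "a full course of quinine or any other appropriate oral treatment (unrelated to the study drugs".
- **Section 4.4 (Rescue Treatments)** deals with failures in active follow-up without naming the first or the second. Rescue is "quinine 10 mg/kg orally three times a day for 7 days or an antimalarial treatment according to the country's national guidelines". Children with severe malaria or danger signs go to parenteral quinine instead.

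Neither section refers to the other.

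The child then stays in the study: "After the rescue treatment the patient will still be considered in the passive follow up until completion of the 6-month period". At a later eligible episode, section 3.10.2 says that "the child will be re-treated with the same drug received for the first episode". This serves objective 3 in section 2, which concerns treating a second episode "with the same ACT used for the first one (second active follow-up".

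On national policy, section 1 lists countries that had chosen an artemisinin combination or were about to: "Zambia for AL; Kenya, Rwanda, Uganda and Tanzania might or are about to change to AL". Table 1 in section 3.1 gives the arms at each site.

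**The concern.** Section 3.10.2 keeps the study drugs out of rescue and section 4.4 does not. A clinician faced with a failure would most naturally look under the section titled for rescue, which is the looser one. Where the guideline drug is also a study arm, two sites can treat the same event differently and each can cite the protocol.

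The practical stake is the child. Under section 4.4, a child whose parasites have just survived a study drug may be given that drug again. A lesser stake is objective 3. A child on AL who was rescued with AL and later re-entered would be on a third AL course rather than a second. This is a treatment rule, so no analysis plan can repair it once the drug has been given.

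**Working it through.** No power or sample-size figure is at issue. The check compares the two rules and then makes one count.

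**1. Do the two sections cover the same event?** Yes, for any non-severe failure in the first active follow-up. For failures in the second, only section 4.4 applies, and it has no bar on study drugs.

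**2. Which drugs does each section allow?**

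| Rescue drug | Section 3.10.2 | Section 4.4 |
|---|---|---|
| Quinine | allowed | allowed |
| Guideline drug, oral and unconnected with the trial drugs | allowed | allowed |
| Guideline drug that is a study arm | not allowed | allowed |

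The rules collide only in the last row.

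**3. Is the limit in section 3.10.2 deliberate?** It reads so. The same section sends other children to the local first-line drug: those with ineligible episodes, and those with malaria after the second active follow-up. It therefore treats the first-line drug and a drug outside the trial as different choices, and reserves the stricter one for failures.

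**4. Can the last row occur?** By section 1, Zambia had opted for AL. By Table 1, the arms at Ndola are AQ+AS, DHAPQ and AL. So it can occur at Ndola. Rwanda and Uganda are described only as possible or imminent changes to AL. If they changed, it could also occur at Rukara, Mashesha, Jinja and Tororo, where AL is an arm, but not at Mbarara, where it is not. Section 3.1 shows that arms and policy are linked in Rwanda: AQ+AS was dropped there because "this combination will not be used as first or second line treatment".

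**5. Does another section close the gap?** No. Section 4.1 bars antimalarials during active follow-up, but section 4.4 ends active follow-up at failure. Section 4.1 then bars nothing in the passive phase. The nearest exclusion criterion in section 3.9 covers ongoing prophylaxis only.

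**6. How many children?** Inputs: 170 children per arm per site and day-28 efficacy of at least 90% (section 3.5). If every AL-arm failure at Ndola in the first follow-up were rescued with AL:

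170 × (1 − 0.90) = 17 children.

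Section 3.5 does not say whether 90% is before or after genotyping, and rescue follows any failure regardless of genotype. Over an assumed failure range of 5% to 25%:

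- 170 × 0.05 = 8.5, about 9
- 170 × 0.25 = 42.5, about 43

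These are ceilings, because quinine meets both sections. No count can be made for the second follow-up, because the protocol does not say how many second episodes it expects.

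**The case against.** The best defence is that the two sections can be read together. Quinine satisfies both and is named first in both. Section 3.10.2 is the stricter and more specific rule for first-follow-up failures, so a careful site would let it govern. Section 1 reports treatment policy, not rescue policy, so AL as rescue is an inference. Most of this stands, and it is why the point is minor. It does not remove the point: nothing says which section governs, and the second follow-up has only the looser rule.

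A reader might also infer more than the protocol supports:

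- **That the primary results are biased.** TF28U and TF28A of the first follow-up count the failure before rescue begins, so the rescue drug does not alter them.
- **That objective 3 is compromised.** Sections 3.7 and 3.10.2 already allow first-line treatment of ineligible episodes in the passive phase, and section 4.1 disallows nothing there. An extra AL course before re-entry can therefore arise without section 4.4. After a failure in the second follow-up, no further study re-treatment follows.
- **That rescue with AL breaks the 29-day rule.** Section 3.8 says "Re-treatment with the same study drug will be done at an interval of at least 29 days from the first treatment". That governs the re-treatment that opens the second active follow-up, not rescue.
- **That rescue and re-treatment can overlap freely.** No sentence requires rescue to be complete first, but sections 3.10.2 and 4.4 imply that order. Section 4.1 also withdraws from an ongoing active follow-up any child taking another antimalarial. A 7-day course begun on day *d* runs through day *d* + 6, so it reaches day 29 only if *d* is 23 or later. Only failures treated on days 23 to 28 could overlap, on days 29 to 34 at most, and a new eligible episode would also be needed.
- **That the problem spans three countries.** Only Zambia's choice is stated as made.

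**Conclusion.** The inconsistency is real, and section 4.4 is wrong as written. It permits, without requiring, what section 3.10.2 forbids, including rescue with the failed drug. The size is small: at most about 17 AL-arm children at Ndola, given 10% failure, AL as the Zambian guideline drug for rescue, and every rescue using it. The figure would be about 9 to 43 at an assumed 5% to 25% failure. The protocol gives no basis for a size or direction of any effect on objective 3. The case for change rests on patient safety and on one consistent rule across sites. Confidence is high for the mismatch in wording and lower for how often it would matter.

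**What to change.** Amend section 4.4 to read: *quinine, or a national-guideline antimalarial that is not a study drug at that site*. Use the same words in section 3.10.2, so that one rule covers failures in both active follow-ups. This sets the bar at site level. Section 3.10.2 can be read as barring all four trial drugs everywhere; if the sponsor intends that, both sections should say so.

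The cost is wording only, with no extra patients, visits or data fields. Where the guideline drug is a study arm, the site falls back on quinine: 3 × 7 = 21 doses over 7 days, against the six-dose AL regimen described in section 1.1. That would concern about 17 children per arm at such a site at 10% failure.

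A sentence in section 3.8 that rescue must be complete before re-treatment would be a useful clarification. It is optional, because sections 3.10.2, 4.1 and 4.4 largely cover it.
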